### Statistical analyses

The data will be analysed using SPSS version 17.0 software and SAS/STAT® version 9.2.

The primary (i.e., adherence CRS score) and secondary (i.e., decisional conflict, satisfaction with care, involvement in decision making, beliefs about treatment, therapeutic relationship, knowledge about information for medical decision and clinical outcomes) endpoints will be analysed on the individual patient level using cluster level summaries, which will account for the correlation between patients in the same ward. The endpoint scores will be compared between control and intervention arms. No interim analysis is planned.

The primary analysis will be performed on the intention-to-treat population corresponding to all included individuals in each participating wards. A secondary analysis will be performed on the per-protocol population corresponding to all included individuals who complete the CRS questionnaire.

Descriptive analyses will provide wards and patient characteristics for each group (control and intervention) at baseline. All analyses will account for clustering to ensure correct type I error rates and confidence intervals [47]. Appropriate statistical methods to account for clustering between patients in the same cluster will be performed using linear mixed-effects models or generalized estimating equations with inclusion of random effects for individual wards and assessment of possible confounding.

The primary endpoint (CRS at 12 months) will be analysed without adjustment by comparison of CRS scores between the two groups using Student t-tests or Mann–Whitney tests according to the variable distribution. A set of secondary analyses will be adjusted for covariates of clinical interest using generalized linear mixed regression models including the group (control/intervention), wards and individuals (as random variables), and other potential confounding variables. These models will be performed using the MIXED SAS procedure (version 9.2). The same procedure will be performed on the secondary endpoints.

Generalized linear mixed regression models will be performed to assess the sustainability of the effect by comparison of monthly means of CRS scores collected during period of the study.

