#### Secondary outcome

As outlined above, there is an interest in studying the difference between the 2 groups of patients in terms of adherence to maintenance drug therapy based on other measures (self-assessment scale and plasma levels of mood stabilizers). Additionally, other dimensions will be assessed: decisional conflict, satisfaction with care and involvement in decision-making, beliefs about treatment, therapeutic relationship, knowledge about information for medical decision, clinical outcomes (depression, mania, functioning and quality of life) and feasibility of SDM processes in clinical practice.The most reliable measurement of patient’s adherence is a multi-method approach that combines feasible self-reporting and reasonable objective measures [27]. Self-evaluation of medication adherence, collection of plasma levels of ongoing mood stabilizers and record of cancelled consultations also will be collected to improve reliability of the patient’s adherence measure. Patients will complete the Medication Adherence Rating Scale (MARS), a self-assessment scale consisting of 10 items assessing behaviours, attitudes and treatment experience. The psychometric properties of this scale are considered satisfactory in BD patients [28] and its French version has been validated [29].Decisional conflict. Patients will complete the Decision Conflict Scale, a self-assessment questionnaire already validated in French and adequate in measuring patient’s perceptions of uncertainty in the choice of a therapeutic option, modifiable factors contributing to this uncertainty but also to an effective decision-making [30, 31]. It is a 16-items scale, with each item rated from 0 to 4 depending on the degree of agreement or disagreement.Satisfaction with care and involvement in decision-making. As there is no validated French scale available for measuring satisfaction with treatment and the decision-making process for outpatients, a questionnaire has been adapted using the Hospitalized Patient’s Satisfaction Scale and the Clinical Decision-making Involvement and Satisfaction Scale (CDIS) [32, 33]. The latter is a new instrument that considers three items on satisfaction with care, and another three items on satisfaction with the medical decision-making process. All items are rated on a scale of 1 to 5, depending on the degree of agreement or disagreement.Beliefs about treatment. Patients will complete the Beliefs about Medicines Questionnaire (BMQ), a validated 18-items scale meant to assess beliefs about medications in patients with chronic disorder [34]. Its psychometric properties are adequate and the French version has already been validated in populations of patients suffering from BD, schizophrenia or major depressive disorder [35, 36]. The questionnaire includes two different scales: a specific scale assessing patient’s beliefs about the specific treatment of the disease being studied, and a general scale evaluating general beliefs about drugs.Knowledge. Patients will complete the Knowledge questionnaire, a tool developed by the Ottawa Research Institute [37] and adapted for BD patients to assess patient’s levels of knowledge considered essential for making medical decisions. Every item can be rated and total score is calculated by converting true answers into percentages.Another aspect of interest will be the evaluation of clinical outcomes in the two groups. During each visit, various aspects of the BD will be assessed: 1. number, duration and type of mood episodes; 2. number and duration of psychiatric hospitalizations; 3. depressive and manic symptoms severity; 4. quality of life and functioning.Depressive symptomatology will be assessed using the French version of the Montgomery-Asberg Depression Rating Scale (MADRS) [38, 39]. This 10-item scale rates various domains such as mood, sleep, appetite, physical and psychic fatigue and ideas of suicide with a score between 0 and 60. Patients also will complete the French version of the Young Mania Rating Scale (YMRS), a validated 11-item scale to assess manic symptoms, with a total score between 0 and 60 [40, 41].Psychosocial functioning will be assessed using the Functioning Assessment Short Test, an instrument designed to assess the main functioning problems experienced by psychiatric patients, particularly BD patients [42, 43] This 24-item scale evaluates impairment or disability in six specific areas: autonomy, occupational functioning, cognitive functioning, financial issues, interpersonal relationships and leisure time. The total score varies between 0 and 72, and a score of 11 or higher defines overall functional impairment.Patients’ well-being and quality of life will be evaluated using the 26-item version of the World Health Organization (WHO) Quality of Life scale (WHOQOL-BREF). This questionnaire covers 4 dimensions of health-related quality of life: physical health (seven items), psychological health (six items), social relationships (three items), environment (eight items), and two global HRQoL items assess an individual’s overall satisfaction with life and a general sense of personal well-being. The scale has good psychometric properties and has been validated in French. All items are rated on a scale of 1 to 5, and total scores range between 0 (worst) and 100 (best) [44].To evaluate feasibility of the SDM process implementation, consultation duration will be measured. Practitioner satisfaction and decisional conflict will be assessed using the questionnaires previously described (the Decision Conflict Scale and the adapted questionnaire for Satisfaction with care and involvement in decision making).

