
### Sample size calculation

The sample size was calculated using PASS Power Analysis and Sample Size Software 15.

The number of subjects required was determined from the assumptions based on the primary outcome, the adherence score measured from the CRS (score rated between 1 and 7).

A minimum difference of 1 point between the two groups is considered as clinically relevant (minimal clinically observable change) [21, 22]. A sample size of 5 clusters per group with 23 individuals per cluster achieves 90% power to detect a difference of 1 between the two group means when the standard deviation is 1.4 and the intra-cluster coefficient is 0.05 using a two-sided T-test with a significance level of 0.05 [45, 46]. To prevent 20% of dropout at 12 months, 30 individuals per cluster is necessary and a total of 300 patients should be included.

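### The primary analysis names all included patients, but its 12-month test can use only those with a score unless missing values are imputed, and the per-protocol set is really a completer set

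*Protocol article*

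**What the plan says.** All of the following is in the protocol article.

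- **Primary population** (Statistical analyses): "The primary analysis will be performed on the intention-to-treat population corresponding to all included individuals in each participating wards".
- **Secondary population** (same section): "A secondary analysis will be performed on the per-protocol population corresponding to all included individuals who complete the CRS questionnaire".
- **Primary test** (same section): "The primary endpoint (CRS at 12 months) will be analysed without adjustment by comparison of CRS scores between the two groups", by Student t or Mann–Whitney test depending on the distribution.
- **Sample size** (Sample size calculation): "A sample size of 5 clusters per group with 23 individuals per cluster achieves 90% power", and then "To prevent 20% of dropout at 12 months, 30 individuals per cluster is necessary and a total of 300 patients should be included".
- **Visits** (Outcomes measures): the same data, CRS included, are collected at baseline and at 3, 6, 9 and 12 months.
- **Sustainability of effect** (Statistical analyses): mixed models for a "comparison of monthly means of CRS scores collected during period of the study".
- **Exclusions after inclusion** (Participants): withdrawn consent and a revised bipolar diagnosis are listed as exclusion criteria, separately from the non-inclusion criteria.

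**The concern.** The named primary population and the named primary test do not fit together. A two-sample test of 12-month scores needs a 12-month score, so some included patients cannot enter it unless their values are supplied by some method. The set meant to complement it is defined by having the outcome, not by what the patient received. A patient in an intervention centre who never saw the decision aid counts as per-protocol if a CRS was recorded. A patient who went through the whole process but missed the rating does not.

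Adherence is the endpoint, and patients who stop attending may well differ in adherence. If losses also differ between arms, a comparison of those who remain is biased. The secondary analysis would not reveal this, because it would rest on much the same patients.

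**Working it through.** **1. The plan's own power figure.** Inputs from Sample size calculation: 5 clusters per arm, 23 patients per cluster, difference 1, SD 1.4, intra-cluster coefficient 0.05, two-sided 0.05.

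- Design effect = 1 + (23 − 1) × 0.05 = 2.10
- Standard error = 1.4 × √(2 × 2.10 / 115) = 0.268
- Noncentrality = 1 / 0.268 = 3.74; df = 2 × (5 − 1) = 8
- Power = 0.904, against 90% stated. It reproduces, and 23 is the smallest cluster size that reaches 90%.

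**2. What the dropout allowance implies.** 23 / (1 − 0.20) = 28.75, so 29 per cluster would do. The plan's 30 is slightly conservative. After 20% loss, 30 × 0.80 = 24 per cluster remain, or 240 of 300, and 60 have no 12-month CRS. The calculation adds patients to replace dropouts, so it treats dropouts as giving no primary data.

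**3. Power is not the problem.** On the same formula, power is 0.909 with 24 per cluster (design effect 2.15) and 0.931 with all 30 (design effect 2.45).

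**4. Who enters each analysis at 20% dropout.**

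| Analysis | Defined population | Usable by the named 12-month test without imputation |
|---|---|---|
| Primary (ITT) | all 300 included | 240 |
| Secondary (per-protocol) | those who complete the CRS, visit not named | the same 240, if completion means at month 12 |

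**5. Size of a possible bias.** None of these inputs is in the documents.

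*Simple form.* Let completers score g points above dropouts in both arms, with dropout proportions d. The completer difference minus the full difference is g × (d_SDM − d_CAU).

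| d_SDM / d_CAU | g | Shift |
|---|---|---|
| 20% / 20% | 1 | 0 |
| 15% / 25% | 0.5 | −0.05 |
| 15% / 25% | 1 | −0.10 |
| 10% / 30% | 1 | −0.20 |
| 10% / 30% | 2 | −0.40 |

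The sign reverses if the intervention arm loses more patients.

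*Dropout driven by the month-9 score.* Assume normal scores with SD 1.4, means 5 (control) and 6 (intervention), month-9 to month-12 correlation 0.6, and dropout that depends on whether the month-9 CRS is below 5. The rise in an arm's completer mean is 0.6 × 1.4 × φ(z) × (difference in retention) / (overall retention), where φ is the standard normal density, φ(0) = 0.399 and φ(1/1.4) = 0.309.

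- Dropout 10% (5 or above) and 30% (below 5) in control, 10% and 20% in intervention, so about 20% vs 12% overall. Control: 0.6 × 1.4 × 0.399 × 0.20 / 0.80 = 0.084. Intervention: 0.6 × 1.4 × 0.309 × 0.10 / 0.876 = 0.030. Estimated difference = 1 − 0.084 + 0.030 = 0.95.
- Dropout 10% and 40% in control, 5% and 20% in intervention, so about 25% vs 9% overall. Control: 0.6 × 1.4 × 0.399 × 0.30 / 0.75 = 0.134. Intervention: 0.6 × 1.4 × 0.309 × 0.15 / 0.914 = 0.043. Estimated difference = 1 − 0.134 + 0.043 = 0.91.

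In simulations with control means of 4 to 5.5 and correlations of 0.4 to 0.8, the two cases ran 0.93–0.99 and 0.88–0.96. With the intervention arm losing more low adherers, the estimate was 1.04–1.08. A shift of 0.05 to 0.09 is about 0.2 to 0.35 of the planned standard error of 0.268.

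**The case against.** On paper the two populations differ: one is everyone included, the other is those with a CRS. A reader might infer that they are the same patients and that a fifth of the sample is silently dropped. The document does not say so. They coincide only if missing 12-month scores are not imputed and completion means at month 12, and neither is stated. Missing-data rules are commonly left to a full protocol or SAP, which is not shown, and 20% is a planning allowance. This objection stands, and the point is conditional for that reason.

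A reader might also infer that the plan itself regards missing patients as less adherent, because a "record of cancelled consultations also will be collected to improve reliability". That section only adds a measure of adherence. Data collection and the Discussion separate care by practitioners from assessment by evaluators, so a missed CRS is not a cancelled care consultation. Informative dropout is plausible but not asserted.

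Nor is the monthly-means model clearly the only longitudinal one. The adjusted secondary models carry a random effect for individuals, which suggests repeated measures. The section also names mixed models and generalized estimating equations in general terms. Still, the sentence on the primary endpoint names the t or Mann–Whitney test.

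Finally, the bias figures are small and rest on assumed inputs, including the control mean. Both worked cases have overall dropout of about 16 to 17%, not 20%. It would also be too much to say that interim scores recover most dropouts, since no dropout timing is given.

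None of this rescues the per-protocol definition, which is stated and contains no criterion for treatment received.

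**Conclusion.** The point holds in conditional form and should be addressed. The test named for the primary endpoint cannot use the whole named population unless missing scores are imputed. At the planned dropout, about 60 of 300 patients would add nothing to it, and the sample size calculation is consistent with that reading. Independently of any imputation rule, the per-protocol set is mislabelled: it is defined by outcome availability, names no visit, and cannot show the effect of the assigned process as delivered.

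The consequence is possible bias, with little loss of power. The bias needs dropout that is related to adherence and that operates differently in the two arms. Its direction is not known in advance. Under the assumptions shown, roughly 0.05 to 0.1 point against the 1-point target is a fair illustration; larger values need more extreme differences in dropout.

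Two inconsistencies belong with this. Monthly CRS means cannot be formed from three-monthly visits, and the exclusions after inclusion conflict with a primary population of everyone included.

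**What to change.** - **Primary analysis.** Use a linear mixed model on CRS at 3, 6, 9 and 12 months from all included patients. Include arm-by-visit terms, baseline CRS, a centre random effect, within-patient correlation, and a small-sample degrees-of-freedom correction for 10 clusters (Kenward–Roger, for example). Take the 12-month contrast as the primary estimate.
- **Sensitivity.** Add a delta analysis that lowers missing 12-month scores, for example by 1 and 2 points, in both arms and in each arm alone. Include patients with no post-baseline CRS, who would not inform the mixed model when baseline is a covariate.
- **Populations.** Rename the present per-protocol set completers at 12 months. Define a true per-protocol set by delivery of the assigned process only if use of the decision aid and personal guide is recorded. Data collection mentions only ongoing treatment and consultation duration after each consultation, so this part may need new data.
- **Wording.** Replace the monthly means with the 3-, 6-, 9- and 12-month visits. State whether patients who withdraw consent or whose diagnosis is revised remain in the primary population, and up to what point their data are used.

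The model needs no new visits, and the SAS MIXED procedure is already named. The cost is modest extra programming and a missing-at-random assumption, which the delta analysis probes but cannot verify.

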**Methods/Design:**

This is a 12-month multi-centre, cluster-randomized controlled trial comparing the efficacy of SDM to CAU. Adult BD patients (*n* = 300) will be eligible after stabilization for at least 4 weeks following an acute mood episode. The intervention will consist of applying the standardized SDM process as developed by the Ottawa Hospital Research Institute in order to choose the maintenance treatment of BD. A multidisciplinary team developed a decision aid “choose my long-term treatment with my doctor” for BD patients to clarify possible therapeutic options. Primary outcome will assess the patient’s level of adherence (based on hetero-evaluation) of ongoing treatment at 12 months. Secondary outcomes will assess the difference between the 2 groups of patients in terms of adherence to maintenance drug therapy based on other measures (self-assessment scale and plasma levels of mood stabilizers). Additionally, other dimensions will be assessed: decisional conflict, satisfaction with care and involvement in decision making, beliefs about treatment, therapeutic relationship, knowledge about information for medical decision and clinical outcomes (depression, mania, functioning and quality of life).

The primary endpoint will be analysed without adjustment by comparison of adherence scores between the two groups using Student *t*-tests or Mann–Whitney tests according to the variable distribution. A set of secondary analyses will be adjusted for covariates of clinical interest using generalized linear mixed regression models.

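### The protocol article contradicts itself on the primary test: the only test named for 12-month CRS has no cluster term and no stated unit, and run on patients' scores it would have about 17–18% type I error

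*Protocol article*

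**What the plan says.** Under Allocation procedures, whole centres are randomised. Study design gives 10 hospitals. Sample size calculation states: "A sample size of 5 clusters per group with 23 individuals per cluster achieves 90% power" for a 1-point difference, with standard deviation 1.4 and intra-cluster coefficient 0.05, "using a two-sided T-test with a significance level of 0.05".

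Statistical analyses then describes the primary comparison in several places:

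- The opening says that primary and secondary endpoints will be "analysed on the individual patient level using cluster level summaries", and that this handles the correlation between patients in the same ward.
- A general statement follows: "All analyses will account for clustering to ensure correct type I error rates and confidence intervals". The next sentence names linear mixed models or generalized estimating equations as the means.
- The one sentence that names the test for the primary endpoint reads: "The primary endpoint (CRS at 12 months) will be analysed without adjustment by comparison of CRS scores between the two groups using Student t-tests", with Mann–Whitney as the alternative if the distribution calls for it.
- Covariate-adjusted mixed models with wards and individuals as random effects are introduced as a set of secondary analyses.

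The Abstract (Methods/Design) carries only the plain version: "The primary endpoint will be analysed without adjustment by comparison of adherence scores between the two groups", again by Student t or Mann–Whitney, with mixed models reserved for secondary analyses.

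**The concern.** The statements do not settle the unit of the primary test. The opening phrase names two units at once, patient and cluster summary. The sentence naming the test speaks of CRS scores in two groups and mentions neither centre means nor a centre effect. An ordinary two-group t-test or Mann–Whitney on patients' scores cannot allow for clustering, so on that reading it breaks the section's own promise of a correct type I error.

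This is not a detail left to an analysis plan: the article does name the primary test, and its statements about it conflict. At stake are the validity of the primary p-value and confidence interval, and a free choice between analyses that can disagree, in a trial where participants, practitioners and investigators are unblinded.

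**Working it through.** **Inputs** (Sample size calculation unless noted): K = 5 centres per arm; m = 23 analysed per centre; difference 1; SD 1.4; ICC 0.05; two-sided alpha 0.05. Enrolment is 30 per centre with 20% dropout, so 30 × 0.8 = 24 may be analysed. The intention-to-treat definition (Statistical analyses) covers all included individuals, so m = 30 is also shown.

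**Step 1: reproduce the stated 90% power.**

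- Design effect: DE = 1 + (m − 1) × ICC = 1 + 22 × 0.05 = 2.10.
- Standard error of the difference: SE = SD × √(2 × DE / (K × m)) = 1.4 × √(4.20 / 115) = 0.2675.
- Noncentrality: 1 / 0.2675 = 3.74.
- Noncentral t with 2(K − 1) = 8 df: power 90.4%. This matches the plan.
- Same SE with patient-level df, 2 × 115 − 2 = 228: 96.1%. Normal approximation: 96.2%. Neither matches.

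The trial was therefore sized with between-centre degrees of freedom.

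**Step 2: type I error if the named test is run on patients' scores.** Ignoring centre understates the variance of the difference by the factor DE, so the error is about 2 × (1 − Φ(1.96 / √DE)).

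| m per centre | ICC | DE | Type I error |
|---|---|---|---|
| 23 | 0.05 | 2.10 | 17.6% |
| 24 | 0.05 | 2.15 | 18.1% |
| 30 | 0.05 | 2.45 | 21.1% |
| 23 | 0.01 | 1.22 | 7.6% |
| 23 | 0.02 | 1.44 | 10.2% |
| 23 | 0.10 | 3.20 | 27.3% |
| 24 | 0.10 | 3.30 | 28.1% |

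The ICC values other than 0.05 are assumptions to show the range. At ICC 0.05 and m = 23, the nominal 95% interval covers 100 − 17.6, or about 82%.

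**Step 3: check by simulation under no effect** (ICC 0.05; 20,000 trials, of which 12,000 for Mann–Whitney).

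| m | t, patients | Mann–Whitney, patients | t, centre means |
|---|---|---|---|
| 23 | 17.8% | 17.1% | 4.9% |
| 24 | 18.6% | 17.8% | 5.3% |
| 30 | 20.9% | 20.8% | 5.0% |
| 23, scores rounded and limited to 1–7 | 17.3% | 17.3% | 5.2% |

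**Step 4: Mann–Whitney on five against five centre means.** By exact enumeration its size is 3.2% at nominal 5%, and the smallest possible two-sided p-value is 0.0079. It is valid but conservative.

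**Step 5: where the readings part** (m = 23).

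- Patient-level t: significant from 1.97 × 1.4 × √(2/115) = 0.36 points.
- Centre-level t with 8 df: significant from 2.306 × 0.2675 = 0.62 points.

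On the planning assumptions, an observed difference between 0.36 and 0.62 points would be positive on one reading and negative on the other.

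**The case against.** The strongest reply is that the section disclaims the patient-level reading. It says that cluster summaries will be used and that all analyses will respect clustering, and neither statement exempts the primary endpoint. The phrase about no adjustment stands against the next sentence on covariates, so it plausibly means only that no covariates enter. The sample size also names a t-test and reproduces with 8 df, which suggests that a centre-level t-test was meant throughout. The mixed-model sentence can be read as belonging to the adjusted analyses.

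Much of this stands. A t-test on centre means is a possible reading, and it would be sound. Three stronger inferences are therefore not supported:

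- That the trial will ignore clustering. The text permits this but does not say it.
- That the test in the Abstract is not the one that was sized. The Abstract gives no unit, so this cannot be established. Nor does 8 df single out centre means: with equal cluster sizes, a mixed model with a centre random effect and 8 between-centre df gives essentially the same test.
- That the plain test carries over to every secondary endpoint. The remark that the same procedure applies to them directly follows the mixed models and may refer only to those.

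The reply does not remove the contradiction. The opening phrase still names the individual patient as the level of analysis, the test sentence still speaks of scores and not of means, and choosing the test by the variable's distribution fits patient scores better than ten means.

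**Conclusion.** The point holds as a contradiction about the primary test that must be resolved before analysis. One permitted reading more than triples the false-positive rate: about 17–18% instead of 5% with 5 centres per arm, 23–24 patients analysed per centre and ICC 0.05, and about 21% if all 30 per centre are analysed. The other reading, a t-test on centre means, holds about 5% and agrees with the 90% power. The inflated figure depends on a patient-level analysis and on the ICC (about 10% at 0.02, 27–28% at 0.10). It does not describe what the trial will certainly do. The sample size calculation itself is sound on this point.

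**What to change.** In the Abstract and in Statistical analyses, name one primary test that respects the randomised centres. Either of these would serve:

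- a two-sample t-test on the ten centre means of 12-month CRS (8 df), with its confidence interval, which matches the sample size; or
- a linear mixed model with a centre random effect and small-sample degrees of freedom.

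Then align the rest of the text:

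- Remove the reference to the individual patient level from the opening sentence of Statistical analyses.
- Say that the absence of adjustment means no covariates.
- State that no t-test or Mann–Whitney that ignores centre will be used for inference on the primary endpoint or, if the same procedure is meant to include these tests, on the secondary endpoints.
- Use the randomised centre as the cluster throughout; Statistical analyses speaks of wards, whereas Allocation procedures randomises centres.

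The cost is wording only. Intervals will be wider than under a patient-level test. The sample size and data collection do not change.

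### Numbers of mood episodes and hospitalisations are sent down the CRS analysis route, where PROC MIXED cannot fit the generalised models named and the unadjusted test uses no follow-up time

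*Protocol article*

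**What the plan says.** The Statistical analyses section lists the secondary endpoints and ends the list with clinical outcomes. For the CRS at 12 months it sets an unadjusted t-test or Mann–Whitney test, chosen by distribution. Adjusted generalised linear mixed models follow, with group, wards and individuals as terms. On software it states: "These models will be performed using the MIXED SAS procedure (version 9.2". The next sentence carries this over: "The same procedure will be performed on the secondary endpoints". The primary analysis set is every included individual.

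Under Secondary outcome, the clinical outcomes to be evaluated in the two groups begin with "number, duration and type of mood episodes; 2. number and duration of psychiatric hospitalizations". Aims and hypothesis expects fewer recurrences with the intervention, and the Discussion names relapse rates among the secondary outcomes.

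The Sample size calculation allows for loss to follow-up: "To prevent 20% of dropout at 12 months, 30 individuals per cluster is necessary". No section mentions a count distribution, person-time or an offset.

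**The concern.** Two things do not fit together.

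- **Model and procedure.** The article names generalised mixed models but assigns them to a procedure that fits only normal-response linear mixed models. PROC MIXED has no log link, count distribution or offset. For a scale score such as the CRS, this is a matter of wording. For event counts, it removes the model that would suit them.
- **Exposure.** A patient who leaves at month 4 can contribute only four months of episodes. If 12-month totals are compared across all included patients, the arm that loses more patients appears to relapse less.

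The trial is open and randomises whole centres, so retention could differ by arm. At stake is the answer on recurrence, which is a stated hypothesis of the trial although a secondary outcome.

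**Working it through.** **1. The plan's own figure.** The Sample size calculation states: "A sample size of 5 clusters per group with 23 individuals per cluster achieves 90% power". Its inputs are a 1-point gap in mean CRS, SD 1.4, ICC 0.05 and two-sided alpha 0.05.

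- Design effect: 1 + (23 − 1) × 0.05 = 2.10.
- Effective n per arm: 5 × 23 / 2.10 = 54.8.
- Non-central t with 2 × (5 − 1) = 8 degrees of freedom: power 0.904.
- Dropout: 23 / 0.8 = 28.75, so 29 would do. The stated 30 leaves 30 × 0.8 = 24 per cluster.

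The 90% and N = 300 stand. Both rest on the CRS alone and say nothing about the counts.

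**2. Expected bias in raw totals.** Assume equal true rates, a proportion d dropping out, and dropout times uniform over the year. Mean follow-up is then (1 − d) × 1 + d × 0.5 = 1 − d/2 years. The ratio of mean totals between arms is (1 − d₂/2) / (1 − d₁/2).

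| Dropout d₁ / d₂ | Ratio of raw means | Apparent effect with none present |
|---|---|---|
| 20% / 20% | 0.900 / 0.900 = 1.000 | none |
| 15% / 25% | 0.875 / 0.925 = 0.946 | about 5% lower |
| 10% / 30% | 0.850 / 0.950 = 0.895 | about 11% lower |

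Only the overall 20% is in the article. The splits by arm are illustrative.

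**3. Simulation.** There were 150 patients per arm (300 / 2) and 1,000 runs per scenario. Counts were negative binomial, with uniform dropout times and no clustering. The control rate (0.5 or 1.0 per year), the dispersion (0.5 or 1.0) and the rate ratio of 0.6 are assumptions. Each cell shows the rejection rate for Welch t-test / Mann–Whitney / negative binomial with log follow-up offset.

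| Rate, dispersion | Dropout 20%/20%, rate ratio 0.6 | Dropout 30% control, 10% intervention, rate ratio 1 | Dropout 30% control, 10% intervention, rate ratio 0.6 |
|---|---|---|---|
| 0.5, 0.5 | 0.65 / 0.62 / 0.66 | 0.09 / 0.10 / 0.06 | 0.44 / 0.39 / 0.66 |
| 0.5, 1.0 | 0.57 / 0.52 / 0.60 | 0.06 / 0.06 / 0.04 | 0.38 / 0.32 / 0.59 |
| 1.0, 0.5 | 0.88 / 0.81 / 0.89 | 0.12 / 0.13 / 0.06 | 0.68 / 0.56 / 0.89 |
| 1.0, 1.0 | 0.77 / 0.68 / 0.79 | 0.10 / 0.13 / 0.05 | 0.57 / 0.44 / 0.80 |

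- **Equal dropout.** Against the offset model, the t-test loses about 1 to 3 power points, close to the simulation error of about 1.5 points. Mann–Whitney loses about 5 to 11. With no true effect, type I error was 0.04 to 0.06 for all three methods.
- **Unequal dropout, no effect.** The raw ratio was 1.11 to 1.13, in line with 0.950 / 0.850 = 1.118 from step 2. Type I error rose to as much as 0.12 (t-test) and 0.13 (Mann–Whitney), against 0.04 to 0.06 with the offset.
- **Unequal dropout, rate ratio 0.6.** The raw ratio was 0.66 to 0.68, against 0.59 to 0.60 with the offset. The power loss was about 20 to 23 points (t-test) and 27 to 37 (Mann–Whitney).

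The dispersion was treated as known, which slightly favours the negative binomial model.

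**The case against.** **The routing is inferred.** No sentence in the analysis section names episodes or hospitalisations. The Abstract and one sentence under Secondary outcome describe clinical outcomes as depression, mania, functioning and quality of life, which are all scales. This stands as a caveat. However, the same Secondary outcome section puts the counts first among the clinical outcomes, and the Discussion makes relapse rates a secondary outcome. The carry-over sentence exempts nothing.

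**A count model is not excluded.** The article names generalised mixed models and GEE, and its abbreviations include a hierarchical generalised linear model. That is fair: the intention may be sound. The obstacle is the named procedure, and the carry-over sentence follows directly on it.

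**Exposure may enter by another way.** A reader might infer that every named procedure ignores follow-up time. The article does not support that. Data are collected every 3 months, and the adjusted models include individuals as a random effect, which suggests repeated rows per patient. With one row per attended interval, a dropout contributes only attended intervals, and equal rates give an expected ratio of about 1. The bias therefore belongs to the unadjusted comparison of 12-month totals in all included patients. Restricting that comparison to completers also removed it in the simulation (t-test type I error 0.04 to 0.06), but the stated analysis set is everyone included.

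**Unequal dropout is not in the document.** Correct. Event rates and dispersion are not given either.

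**Conclusion.** The point holds in limited form. The firm part is textual: the adjusted analysis names a model class that PROC MIXED cannot fit to counts, and the unadjusted comparison applied to those counts contains no follow-up time despite an expected 20% dropout.

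The size of the harm is conditional. Raw totals are off by about 5% at 15% versus 25% dropout and about 11% at 10% versus 30%, given equal true rates and uniform dropout times. At the wider split, simulated type I error reached 0.12 to 0.13. All of this rests on dropout differing by arm, on assumed rates and dispersion, and on simulations without clustering.

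A reader might also infer a general loss of precision. The figures do not support that for the t-test under equal dropout, where the loss is negligible; it is moderate only for Mann–Whitney. Nor does the point reach the primary CRS result or the sample size. It is a secondary-outcome correction, worth making because recurrence is a stated hypothesis and the change is cheap.

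**What to change.** Limit the t-test/Mann–Whitney and PROC MIXED route to scale scores. For the numbers of mood episodes and psychiatric hospitalisations, state a Poisson or negative binomial mixed model (or GEE) with log follow-up time as offset and centre as the cluster. Fit it in a procedure that supports this, such as PROC GLIMMIX, and report rate ratios with 95% CI.

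The cost is analysis wording and a different SAS procedure. The 3-monthly visits should already supply follow-up time. There are two small downsides:

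- The model may have trouble converging with 10 centres, so name a comparison of centre-level event rates as the fallback.
- The offset removes the bias only if dropout is unrelated to relapse, and the plan should say so.

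This change covers the two counts only and prescribes nothing for durations.
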